### **2.1.3.2 Secondary efficacy endpoint(s)**

The timing of all secondary endpoints assessments are specified in the study flowchart (in Appendix A).

The secondary efficacy endpoints include:

- Changes in physical performance measures from baseline to Month 24 and Month 36, assessed by:
  - The total SPPB score computed directly in the corresponding e-CRF page (ranging from 0: low performance to 12: high performance)
  - The usual gait speed in m/s, assessed by the ratio of the 4 meters walks divided by time (faster of the two walks of the gait speed test)(see details in [Section 2.5.2](#))
  - The handgrip strength (maximum reading in kg)

- Changes in disability status from baseline to Month 24 and Month 36, assessed by:
  - The Lawton IADL score (ranging from 0 to 8; the higher the score, the greater the participant's abilities) obtained from the Pepper Assessment Tool for Disability (PAT-D) questionnaire computed directly in the corresponding e-CRF page
  - The KATZ ADL score obtained from the PAT-D questionnaire (ranging from 0 [participant totally dependent] to 6 [participant independent])
- Time (in days) from the randomization to the date of first occurrence of persistent mobility disability, operationalized as the failure to complete the 400-metre walk test within 15 minutes or as the assessment of disability by the adjudication in two consecutive visits, or as a first mobility disability followed by the death:
  - Persistent mobility disability will be considered ascertained:
    - at the date of the first test failure among the 2 consecutive available test failures, whatever the time interval between the 2 consecutive visits, if the first test failure is observed no more than 9 months after the previous test success
    - Or at the date of the last available test failure before the date of death, whatever the time interval between the failure and the death, if the test failure is observed no more than 9 months after the previous test success
    - Or at the date of the success test (including baseline test) + 183 days (i.e. months 6) if a persistent disability (i.e. 2 consecutive observed failure tests whatever the time interval between the 2 consecutive visits, or one failure test followed by the death) is observed more than 9 months after the previous test success
  - Participants will be censored:
    - at the date of last available test (failure or success) or date of death if no persistent mobility disability observed and no more than 9 months between two consecutive visits or between the last available successful test and the death,
    - or at the date of the first test (failure or success) where the following test is observed more than 9 months after the previous test, and no persistent disability is observed.

Notes: The baseline assessment is considered as a successful test in this endpoint definition.

If no post-baseline visit is done, then participants will be censored at the date of randomization visit V1-T0 (or date of randomization if V1 is missing).

- Changes in body composition measures from baseline to Month 24 and Month 36, assessed using DXA (centralized reading):

- $aLM^{BMI}$ , in males and females
  - $aLM$  in kg, in males and females
- Changes in anthropometric parameters from baseline to Month 24 and Month 36, assessed by:
  - Weight in kg, assessed using percent change
  - Body mass index (BMI) in  $kg/m^2$ ,
  - Calf circumference in cm,
  - Waist circumference in cm,
  - Hip circumference in cm,
  - Mid-arm circumference in cm
- Changes in nutritional status from baseline to Month 24 and Month 36 assessed by the Mini Nutritional Assessment-Short Form (MNA-SF) score computed directly in the corresponding e-CRF page (ranging from 0 to 14: a score of 12 or greater indicating satisfactory nutritional status and a score strictly below 8 indicating malnutrition)
- Changes in cognitive function from baseline to Month 24 and Month 36, assessed by the Mini Mental State Examination (MMSE) score computed directly in the corresponding e-CRF page (ranging from 0 to 30: a score of 27 or greater indicating normal cognitive function, between 19 and 24 indicating mild cognitive impairment, between 10 and 18 indicating moderate cognitive impairment and a score of 9 or below indicating severe cognitive impairment)
- Changes in Cumulative Illness Rating Scale (CIRS) from baseline to Month 24 and Month 36, computed directly in the corresponding e-CRF page:
  - Total score (ranging from 0 to 56)
  - Severity index (ranging from 0 to 4)
  - Comorbidity index (ranging from 0 to 14)
- Changes in mood from baseline to Month 24 and Month 36 using the Center for Epidemiological Studies-Depression scale (CES-D):
  - The score obtained with the 11-item version of the CES-D will be transformed using the procedure recommended by Kohout (3) to make it compatible with the full 20-item instrument (see details in Section 2.5.2). Total scores range from 0 to 60, with higher scores indicating more depressive symptoms.
- Time (in seconds) to complete the Trail Making Test (TMT) of visuo-motor speed (part A) and executive function (part B)
- 7-day average of total steps, sitting and lying activity (hours), standing activity (hours) and stepping activity (hours), from ActivPal accelerometry

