##### **Secondary efficacy endpoints:**

- Changes in physical performance measures
  - SPPB
  - Handgrip strength
  - ADL
  - Instrumental ADL (IADL)
  - Usual gait speed over 4 metres
  - Pepper Assessment Tool for Disability (PAT-D)
- Changes in body composition measures (assessed using DXA), anthropometric parameters (e.g., body mass index [BMI], mid-arm circumference, calf circumference), and nutritional status (Mini Nutritional Assessment-Short Form, MNA-SF)
- Changes in cognitive function (assessed using MMSE) and mood (i.e., Center for Epidemiological Studies-Depression scale, CES-D)
- Incidence of falls (assessed using self-reported questionnaire and a dedicated technological device)
- Modifications of quality of life (measured using the EuroQoL-5D instrument)
- Differences in use of healthcare services (including outpatient clinics, emergency room admissions, hospitalisations, institutionalisations)
- Mortality rate

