##### **4.3.2. Secondary outcomes**

- a. Changes in physical performance measures
  - Short physical performance battery (SPPB)
  - Handgrip strength
  - Usual gait speed
- b. Changes in disability status
  - Pepper Assessment Tool for Disability (PAT-D)
  - Incidence of persistent mobility disability (operationalised as the failure of completing the 400-metre walk test in two consecutive 6-month visits)
- c. Changes in body composition measures (assessed using Dual Energy X-Ray Absorptiometry, DXA), anthropometric parameters (e.g., body mass index, mid-arm circumference, calf circumference), and nutritional status (Mini Nutritional Assessment-Short Form, MNA-SF)
- d. Changes in cognitive function (assessed using Mini Mental State Examination, MMSE) and mood (i.e., Center for Epidemiological Studies-Depression scale, CES-D)

- e. Incidence of falls (assessed using self-reported questionnaire as well as via a technological device) and injurious falls
- f. Modifications of quality of life (measured using the EuroQoL-5D instrument)
- g. Differences in use of healthcare services (e.g., outpatient clinics, emergency room admissions, hospitalisations, institutionalisations)
- h. Mortality rate

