### 5.1. Eligibility criteria

The eligibility criteria in this study are aimed at identifying persons who are physically frail and sarcopenic, that is have the clinical and biological hallmarks of functional limitation (as assessed by a battery of physical performance tests and DXA). At the same time, candidates for the SPRINTT RCT will also be non-disabled, as documented by their ability to walk 400 metres without sitting or the help of another person. Targeting this subset of the population makes it possible to recruit a non-disabled but at-risk population for a clinical trial of disability prevention. Interestingly, the eligibility criteria to be adopted in SPRINTT are very similar to those already implemented in the recently concluded LIFE study. This will not only allow the positioning of SPRINTT on the solid bases of LIFE, but also possible future comparisons between the two populations and adopted interventions.

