### **7.3.4. Pepper Assessment Tool for Disability**

Self-Reported Physical Function/Disability is assessed with a modified version of disability instrument that was used in the LIFE-P and LIFE trials, now called the Pepper Assessment Tool for Disability (PAT-D). The instrument includes 19 items covering 3 domains: 1) basic ADLs (moving in and out of a chair, moving in and out of a bed, gripping with hands, using toilet, dressing, getting in and out of a car, and bathing); 2) mobility (walking several blocks, lifting heavy objects, walking one block, lifting/carrying 5 kg, climbing several flights of stairs, and climbing 1 flight of stairs); and 3) instrumental ADLs (light housework, participating in community activities, managing money, visiting with relatives or friends, using the telephone, and taking care of a family member).

For each item, respondents answer whether they experience 1) no difficulty, 2) a little difficulty, 3) some difficulty, 4) a lot of difficulty, 5) unable to do or, 6) did not do for other reasons. Answers are averaged across the items in order to better assess the overall perceived disability burden by a person.

As in LIFE-P and LIFE, two items will be added to the disability instrument, giving a total of 21 items. These are “walking across a small room” and “walking 400 meters”. These two items have been used previously as the single outcome of interest for studies on mobility disability. In addition, for the basic ADLs (including walk across a room, but not gripping with hands), we plan to ask whether the participant receives help from another person to complete the task. This will allow us to calculate a Katz ADL score.

A proxy ADL questionnaire is administered when a participant is not available to complete a follow-up assessment.

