Time to first occurrence of persistent mobility disability will be compared, as for the primary analysis endpoint, in the randomized population with a baseline SPPB score <8 within the intervention arm, using a two-sided Log-rank's test stratified by study site and gender. Hazard ratio (and 95% CI) between intervention groups will be estimated using a Cox proportional hazard model with the stratification factors of study site and gender as covariates.

The cumulative incidence functions for the 2 intervention arms will be summarized using Kaplan-Meier method and displayed graphically. The cumulative incidence rate over

time at each scheduled time-points of the protocol together with appropriate 95% confidence interval will be provided.

The time to complete the TMT-A test and the TMT-B test, as well as, the 7-day average of total steps, sitting and lying activity (hours), standing activity (hours) and stepping activity (hours) from ActivPal accelerometry will be summarized by visit using number, median, Q1, Q3, minimum and maximum. In addition, results overtime will be presented graphically using boxplots.

For other efficacy parameters not normally distributed, a non-parametric approach will be used. Descriptive statistics will be summarized using median, Q1, Q3, minimum and maximum.

All secondary endpoints analyses will be provided also in the randomized population with a baseline SPPB  $\geq 8$  assigned by randomization.

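### The SAP analyses disability status without the PAT-D mean score that the protocol promised, does not record the change, and leaves the source of its Lawton score undefined

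*Combined protocol and SAP*

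**What the plan says.** Protocol 4.3.2, item b, measures change in disability status by two things: "Pepper Assessment Tool for Disability (PAT-D") and the incidence of persistent mobility disability. The synopsis also names PAT-D among its secondary efficacy endpoints, next to ADL and "Instrumental ADL (IADL").

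Protocol 7.3.4 describes PAT-D as 19 items in three domains, with two walking items added, and says how to score it: "Answers are averaged across the items in order to better assess the overall perceived disability burden by a person". For the basic ADLs it adds a separate question, "we plan to ask whether the participant receives help from another person to complete the task", from which a Katz score is to be calculated.

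SAP 2.1.3.2 lists two scores under disability status: "The Lawton IADL score (ranging from 0 to 8; the higher the score, the greater" the abilities, and "The KATZ ADL score obtained from the PAT-D questionnaire (ranging from 0 [participant totally dependent] to 6 [participant independent". Both are said to come from the PAT-D form. Persistent mobility disability follows as a time-to-event endpoint. No PAT-D mean or domain score appears as an endpoint anywhere in the SAP; the form is otherwise used only as a source for adjudication. SAP 1.6, the place for modifications made in the SAP, records none.

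**The concern.** The PAT-D mean grades difficulty from none to unable, so it can register change before a person needs help. Katz counts help received with basic ADLs and has seven possible values. Participants live in the community, have an MMSE of at least 24, and can walk 400 m without a walker or another person's help. In such people a count of help received may be coarse, and many may start at the top of it.

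The analysis rule adds to this. SAP 2.4.4.2 models change by MMRM for normally distributed variables, then says: "For other efficacy parameters not normally distributed, a non-parametric approach will be used". Only descriptive statistics are named for that route. If Katz and Lawton were sent there, neither disability score would have a specified between-arm comparison.

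At stake is what the trial can say about change in disability status, one of its stated secondary objectives. The reader of the report would also not learn that the protocol's own disability score had been left out.

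**Working it through.** **Text comparison**

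| Item | Protocol | SAP |
|---|---|---|
| PAT-D mean | Named in synopsis and 4.3.2; scoring in 7.3.4 | Absent |
| Persistent mobility disability | 4.3.2 | Kept, with log-rank test, hazard ratio and cumulative incidence (2.4.4.2) |
| Katz ADL | ADL in synopsis; Katz foreseen in 7.3.4 | Endpoint, 0 to 6 |
| Lawton | IADL in synopsis; no scoring rule | Endpoint, 0 to 8 |
| Declared change | n/a | None in 1.6 |

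**Availability of the data.** The protocol flowchart and SAP Appendix A schedule PAT-D at T0 and months 3, 6, 12, 18, 24, 30 and 36, which is eight time points, plus the end-of-study visit. The schedule is the same in both arms.

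**Scoring gap.** Protocol 7.3.4 numbers six answers and averages them. The sixth, an activity not done for some other reason, is not a grade of difficulty. Suppose a participant answers 1 on 18 items and 6 on one. The raw mean is (18 × 1 + 6)/19 = 24/19 = 1.26. With the sixth option set to missing it is 18/18 = 1.00.

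**Lawton source.** Protocol 7.3.4 lists 7 basic ADL, 6 mobility and 6 instrumental items (7 + 6 + 6 = 19). Six instrumental items counted once each reach 6, not 8, so a 0 to 8 score needs further items or a rule that neither document gives. The SAP writes Lawton IADL in 2.1.3.2 and Lawton ADL in the adjudication algorithm of 2.1.3.1, which it describes as drawing on gait speed and the ADL Proxy and Assistive Device questionnaires. Whether these are the same score is not stated. In that algorithm a value of 8 can stand in for the gait-speed condition when a missing walk test is classified as no disability, provided the walking questions are also answered favourably.

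**Illustration of a possible ceiling.** The documents give no mean, SD or share at maximum for Katz, Lawton or PAT-D, so there is no plan figure to reproduce. Assumed inputs:
- one latent disability trait, with a true arm difference of 0.20 SD;
- item loadings of 0.7 and 0.8;
- PAT-D as the mean of 19 five-level items, with cut-points at the 50th, 75th, 90th and 97th percentiles;
- Katz as a count of 6 yes/no items, with the control-arm share at maximum set to 50% to 95%.

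The number per arm is 600 (SAP 1.4) × (1 − 0.25) (dropout over 2 years, SAP 1.3) = 450. Power is approximately Φ(ES × √(n/2) − 1.96). The ratio of sample sizes is (ES for PAT-D ÷ ES for Katz)².

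Example at 80% and loading 0.7. Katz: 0.111 × √225 − 1.96 = −0.295, power 0.38. PAT-D: 0.183 × 15 − 1.96 = 0.785, power 0.78. The ratio is (0.183/0.111)² = 2.7.

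| Share at Katz maximum | Power, Katz | Power, PAT-D mean | Sample ratio |
|---|---|---|---|
| 50% | 0.58–0.66 | 0.77–0.78 | 1.34–1.55 |
| 70% | 0.48–0.54 | 0.78–0.80 | 1.82–2.07 |
| 80% | 0.38–0.42 | 0.78 | 2.42–2.74 |
| 90% | 0.27–0.31 | 0.80 | 3.66–4.30 |
| 95% | 0.18–0.20 | 0.79 | 6.10–7.20 |

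Each range spans the two loadings. The model compares scores at one time point and assumes that PAT-D itself is not bunched at its lower end, so it shows a direction, not an estimate for this trial.

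**The case against.** Much can be said for the SAP. ADL and IADL are not its invention: the synopsis lists them and protocol 7.3.4 foresees a Katz score. SAP 1.5 is literally correct, since the protocol's statistical section never names PAT-D. Secondary endpoints are exploratory under SAP 2.4.4.3. The Lawton score is said to be computed on an eCRF page that is not in these documents, so a valid rule may exist there. All of this stands. It limits the weight of the point but does not remove it, because the protocol names PAT-D beside ADL and IADL, not as an alternative to them.

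A reader might go further and infer four things that the documents do not support.

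- *Katz and Lawton sit at their ceiling.* The protocol says that "candidates for the SPRINTT RCT will also be non-disabled", but it documents this by the 400-m walk, not by ADL or IADL independence. A cane is allowed and entry requires an SPPB of 3 to 9.
- *A null result would reflect the scale.* The trial aims to prevent decline, and a participant at Katz 6 has the whole scale left to fall. The lower quartile would move once a quarter of an arm declined.
- *Disability status has no between-arm estimate.* Persistent mobility disability has a log-rank test and hazard ratio. SAP 2.4.4.2 never assigns Katz or Lawton to the non-parametric route, and it also promises MMRM least-squares means for all quantitative secondary endpoints.
- *The trial gives up its sensitive measure.* The documents do not report how sensitive PAT-D is to change. Its mean could itself bunch at no difficulty, and the items are still collected.

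**Conclusion.** The point holds in a limited form. It is a fact of the text that the SAP leaves out the PAT-D mean, an outcome the protocol names and scores, and that SAP 1.6 does not say so. It is also a fact that neither document shows how a 0 to 8 Lawton score is obtained.

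A ceiling on Katz is plausible but unproven. The loss in the illustration runs from moderate (about 1.3 to 1.6 times the sample at 50% at maximum) to severe (about 6 to 7 times at 95%), and it rests wholly on assumed distributions.

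The consequence is a thinner answer on change in disability status. The primary conclusion does not depend on the PAT-D omission. The Lawton question does reach the primary endpoint, through the rule for missing walk tests, but the documents do not allow its effect to be sized. The change should be made; it is not a condition for the trial's main result.

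**What to change.** 1. In SAP 2.1.3.2, add change from baseline in the PAT-D mean as a disability-status endpoint beside Katz and Lawton: overall and for the basic ADL, mobility and instrumental ADL domains. State whether the overall mean uses 19 or 21 items, and set the sixth answer option to missing.
2. Analyse it with the MMRM already defined in SAP 2.4.4.2.
3. Record the difference from protocol 4.3.2 and its reason in SAP 1.6.
4. State which items and which form give the 0 to 8 Lawton score, use one name for it, and confirm whether it is the score used in the adjudication algorithm of SAP 2.1.3.1.

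Katz can stay as it is; redefining it as new dependence would be a matter of preference.

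The cost is SAP wording and one more exploratory model, repeated for the domains, on data already scheduled in both arms. There is no new data collection and no effect on the type I error of the primary test.

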### 2.1.4 Safety endpoints

The safety analysis will be based on the reported adverse events and other safety information, such as clinical laboratory data and vital signs.

The observation period of safety data is from the randomization visit V1-T0 or date of randomization if V1 is missing (excluded) until the end of the study.

All measurements of safety information (except adverse events and deaths), scheduled or withdrawal visit (V9), will be assigned to analysis windows defined in Section 2.5.4 in order to provide an assessment of the safety parameters at each post-baseline time point planned to be collected as per protocol.

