**Safety measurements:**

- Assessment of adverse events;
- Clinical examination parameters (i.e. systolic and diastolic blood pressure, pulse rate, body weight, BMI);
- Electrocardiogram (ECG);
- Assessment of biological parameters (i.e. standard blood biochemistry, haematology, urinalysis).

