### **6.3.8. ECG**

A 12-lead ECG is performed at the initial visit for safety purposes. The ECG is reviewed by the study physician at each field centre to assess potential exclusion criteria. In addition, to assess silent myocardial infarction, ECG will be performed at each follow-up and closeout visit, except that at 3 months.

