## **8.6. Data management**

Data are collected via the web-based eCRF and stored in a secured database.

For data collected on paper, the investigator or the designated person will be responsible for data processing. All the data collected on paper will be stored in the investigation centre.

The data manager must make certain that all data is completed on the eCRF and will request correction/clarification from the investigator using electronic data clarifications that should be answered and closed as quickly as possible.

For data collected on the eCRF, the investigation centre will be responsible for data processing including data validation performed according to a specification manual describing the checks to be carried out. Based on data validation, previously entered data may require changes. An electronic data clarification form will be sent to the investigator who will be required to respond to the query and make justified changes. All data are

centralised in the DB and all the data transfers will be automatically managed by Service Bus according to a transfer protocol issued by the data manager.

All the following coding activities medical / surgical history, adverse events, procedures and ECG abnormalities will be performed centrally using MedDRA and for medications using WHO-DD.

The coding process will be described in a specification manual.

When data validation is achieved, a (*blind*) review of the data will be performed according to the SPRINTT standard operating procedure. When the database is completed and accurate, it will be locked and the treatment codes will be unblinded and made available for data analysis.

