| Blood Pressure
SBP > 170mm/Hg or
DBP > 100mm/Hg                                                                                                                                      | Qualified staff should talk to participant, and encourage participant to seek additional follow-up and/or evaluation.                                                                                                                                                                     |
| Resting Pulse
Rate > 100 or < 40 beats/min                                                                                                                                              | Qualified staff should talk to participant, and encourage participant to seek additional follow-up and/or evaluation.                                                                                                                                                                     |
| Abnormal results at the Center for Epidemiological Studies-Depression Scale and/or Mini Mental State Examination questionnaires                                                            | Qualified staff should talk to participant, and encourage participant to seek additional follow-up and/or evaluation.                                                                                                                                                                     |
| MNA-SF score <8/14 (identifying malnutrition)                                                                                                                                              | The result will be forwarded to the participant's PCP regardless of group assignment. For participants randomised to the multi-component intervention, personalised nutritional recommendations will be elaborated and followed up by the local D/N with support from the study physician |
| ECG meets exclusion criteria.
Serious conduction disorder (e.g., 3 rd degree heart block), uncontrolled arrhythmia, or new Q waves or ST-segment depressions (>3 mm) on ECG. | Qualified staff should talk to participant, and encourage participant to seek additional follow-up and/or evaluation.                                                                                                                                                                     |

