rare instances, heart attack, stroke, and death. Cardiovascular events are assessed using standard protocol measures including ECGs. When a cardiovascular event has occurred, the study physician decides whether it is permissible for the participant to continue interventions. If the SPRINTT interventions are discontinued for safety reasons, they may be resumed after consultation with the participant's primary care physician.

Serious fall injuries and fractures are assessed using standard protocol measures, including radiographs and hospital records. When a serious fall injury or fracture occurs, a study physician decides whether it is permissible for the participant to continue interventions. If the SPRINTT interventions are discontinued for safety reasons, they may be resumed after consultation with the participant's primary care physician.

In the SPRINTT safety monitoring system, participants who report adverse events to any staff person at any time are referred to unblinded medical staff responsible for identifying, recording, and managing these events. Safety-related events are reported in a timely fashion as required by the DSMB and the Ethics Committee responsible for the study. Interventionists and other staff reporting or managing adverse events for safety purposes do not at any time communicate information regarding these events to study assessment personnel.

SPRINTT maintains an event outcome record that is completely separate and distinct from the safety monitoring system for the intervention group. This is necessary because many of the SPRINTT staff members are not masked to intervention assignment, and it is critical that the identification and reporting of serious adverse events for safety reasons not bias the study's collection of outcome data. Thus, for outcome purposes, all SPRINTT participants are systematically queried at clinic visits or phone calls according to the protocol to capture outcome data on study outcomes, medical events, or adverse experiences. This separate outcome record contains solely those adverse events that are reported through these interviews conducted by designated outcome assessment staff masked to intervention assignment.

All serious adverse events and deaths shall be reported within 48 hours to DSMB and to the Management Board. All Serious Adverse Events shall be reported in a summary format by the blinded treatment arm (A and B) to the DSMB and Management Board monthly.

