**Appendix B    Vital signs abnormalities and alert**

| ALERT                                          | ACTION                                                                                                         |
|-------------------------------------------------------|-----------------------------------------------------------------------------------------------------------------------|
| Blood Pressure
SBP > 140mm/Hg or
DBP > 90mm/Hg  | Clinic staff inform the participant                                                                                   |
| Blood Pressure
SBP > 170mm/Hg or
DBP > 100mm/Hg | Qualified staff should talk to participant, and encourage participant to seek additional follow-up and/or evaluation. |
| Resting Pulse
Rate > 100 or < 40 beats/min         | Qualified staff should talk to participant, and encourage participant to seek additional follow-up and/or evaluation. |

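### The protocol repeats ECGs from month 6 to look for silent myocardial infarction, but the SAP specifies no ECG variable and no by-arm ECG summary

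*Combined protocol and SAP*

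**What the plan says.** **Protocol.** The synopsis names four safety measurements: adverse events, clinical examination parameters, ECG and biological parameters. The ECG section (numbered 6.3.8, within chapter 7) gives the purpose and timing of the repeat tracings: "to assess silent myocardial infarction, ECG will be performed at each follow-up and closeout visit, except that at 3 months". The alert table in 11.4 has an ECG row covering serious conduction disorder, "uncontrolled arrhythmia, or new Q waves or ST-segment depressions (>3 mm) on ECG". Section 8.6 plans the coding of "procedures and ECG abnormalities will be performed centrally using MedDRA". Section 11.9 names the serious harms expected from exercise as, in "rare instances, heart attack, stroke, and death", and adds: "Cardiovascular events are assessed using standard protocol measures including ECGs".

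**SAP.** Section 2.1.4 opens: "The safety analysis will be based on the reported adverse events and other safety information, such as clinical laboratory data and vital signs". Its subsections cover adverse events, falls, deaths, laboratory variables and vital signs, and vital signs means heart rate and blood pressure. The common rules in 2.4.5 define abnormal values for laboratory tests and vital signs only, and 2.4.5.1 to 2.4.5.5 follow the same five topics. The flowchart in Appendix A keeps the ECG row at screening, months 6 to 36 and end of study.

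**The concern.** At the level of the synopsis's four headings, ECG is the only safety measurement with no planned analysis. A silent infarct causes no symptom and no admission, so a record built from reported events is poorly suited to finding it. The protocol schedules repeat ECGs for that reason.

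This matters for interpretation. Heart attack is the first serious harm the protocol expects from the exercise intervention, and section 11.6.1 explains why participants have no stress test before starting. If the SAP is followed as written, the cardiac safety conclusion rests on events that came to notice and were reported. The tracings meant to find the others are collected and coded but not summarised.

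**Working it through.** No power, alpha or effect size is involved. The check follows ECG through both documents and asks how a silent infarct could reach a by-arm table.

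**1. Is there a direct route?** SAP 2.1.4.1 to 2.1.4.5 contain no ECG variable. The abnormality rules in 2.4.5 are limited to laboratory tests and vital signs, and 2.4.5.1 to 2.4.5.5 contain no ECG table. There is no direct route.

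**2. Is there a route through adverse events?** SAP 2.1.4.1 collects four classes. Take a new Q wave found at a routine visit in a participant without symptoms:

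- *Serious adverse event.* Protocol 11.9 counts a laboratory or clinical test finding judged clinically significant as serious, and an infarct on ECG could meet that. The SAP's list omits the criterion. It keeps death, hospital admission, life-threatening illness or accident, permanent disability, and other serious illness that could have become serious without aggressive treatment. A symptom-free finding need not meet any of these.
- *Adverse event of special interest.* An abnormal diagnostic test counts only if it needs medical attention at once. The protocol's action for an ECG alert is to talk to the participant and encourage further evaluation, so an alert-level ECG need not qualify.
- *Event under staff supervision.* The listed items concern exercise symptoms, out-of-range vital signs, falls, active intervention by staff, illness needing medical management, or an event that is already serious. A chance finding on a scheduled tracing does not clearly fit.
- *Unexpected event possibly related to study procedures.* This depends on a judgement of relatedness, and protocol 11.9 already lists heart attack as an expected harm of exercise.

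Each route is possible and none is assured. Protocol 11.9 says ECGs help assess cardiovascular events, but neither document has a rule that turns a scheduled ECG abnormality into an adverse event record.

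**3. What cardiac information is compared?** SAP 2.4.5.1 tabulates all emergent, serious, special-interest and supervised-session events by arm, by organ class and preferred term, with rates per patient-year. The supervised-session categories include chest pain and dyspnoea persisting after exercise. SAP 2.4.5.3 tabulates fatal events. For SPPB below 8 it also compares time to death with a stratified log-rank test and a Cox hazard ratio. Clinically reported heart attack, stroke and death are therefore covered.

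**4. How much data is left without a summary?** SAP 1.3 gives 1,205 + 314 = 1,519 randomised. By month 24 the schedule has 4 follow-up ECGs (months 6, 12, 18, 24), and by month 36 it has 6 (adding months 30 and 36).

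- 1,519 × 4 = 6,076
- 1,519 × 6 = 9,114

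Both figures assume full attendance and leave out end-of-study tracings. The upper one also assumes that everyone reaches month 36, whereas SAP 1.4 gives a range of two to three years. Dropout lowers both.

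**The case against.** Several points on the other side stand.

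- A reader might infer that the cardiac risk named in the protocol is never compared between arms. That is wrong: step 3 above shows that reported heart attacks, strokes and deaths are presented by arm and that death is tested.
- A reader might infer that Appendix B dropped an ECG row. The appendix is titled "Vital signs abnormalities and alert", and it also leaves out the protocol's alert rows for mood and cognition, nutrition and the tibial artery. It is a vital-signs table, so it shows no error.
- A reader might take SAP 1.6, which reports no statistical modifications, as hiding a change. Protocol section 10 specifies no ECG analysis, and no analysis of adverse events, laboratory data or vital signs either. There was no planned ECG analysis to modify.
- A reader might argue that ECG is the one cardiac measure taken by masked staff on equal terms. Blood pressure and heart rate follow an equal schedule in both arms and are analysed. Protocol 11.9 has masked outcome staff question all participants about medical events. The only ECG review described is local, by the study physician, and nothing says whether that reader is masked.
- The tracing count says nothing about how many infarcts would be missed. The documents give no incidence from which to work that out.

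Two defences do not remove the gap. The SAP's list in 2.1.4 is worded as open-ended, but an open list does not define a variable, a denominator or a table. The protocol's broader definition of a serious event might capture an ECG finding, but the SAP does not carry that criterion into its own list.

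**Conclusion.** The point holds in a limited form. A safety measurement that the protocol names, schedules for a stated purpose and plans to code has no specified variable or by-arm summary in the SAP. Silent infarction and other new ECG abnormalities would be visible only if reported as adverse events, and the SAP's definitions leave that to chance.

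The effect on the safety conclusion cannot be sized from the documents. What can be sized is the unsummarised material, about 6,100 to 9,100 scheduled tracings before dropout. The conclusion assumes that no separate document covers ECG. The SAP refers to separate documents for health economics and biomarkers, but to none for ECG. This should be corrected, but it does not affect the primary efficacy analysis.

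**What to change.** Add an ECG subsection to SAP 2.1.4 and a matching one to 2.4.5.

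- **Variable:** at least one new post-baseline ECG abnormality, using the categories already in protocol 11.4, as recorded and coded in the eCRF. New means absent from the pre-randomisation tracing, in line with the SAP's existing baseline rule.
- **Table:** number and percentage of participants, by arm, separately for SPPB below 8 and SPPB 8 or above, among those with at least one follow-up ECG. Show the denominator.
- **Listing:** participants with new Q waves and no reported infarction.
- **Optional:** a between-arm difference with a 95% confidence interval, labelled descriptive, because apart from death the SAP's safety analyses are descriptive.

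If the sponsor prefers not to analyse ECG, the SAP should say so and give the reason. The addition is prespecified only if made before the database lock planned in SAP section 4; after that it should be labelled post hoc.

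The cost is one subsection, one table and one listing, with no new procedures. Two limits remain. The documents do not show whether the eCRF holds each 11.4 category in a form that can be tabulated, so check this first. Local reading, possibly unmasked, may limit interpretation, and the report should say so.
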